##### Computer-based/psychophysical tests

Six computer-based measures are used in the present study to assess the following neuropsychological functions: visuospatial attention, cognitive representation of space, spatially-defined motor function, and body representation. To test for spatial attention bias in near space, we administer versions of three tasks that have been used to measure spatial attention in hemispatial neglect: a visual Temporal Order Judgement (TOJ) task [8], a Landmark task [54], and a Greyscales task [55]. The fourth task is a Mental Number Line Bisection task, which measures the mental representation of space [56, 81]. The fifth task is a Directional Hypokinesia task, a measure of motor “neglect-like” impairment. The final computer-based task is a Hand Laterality Recognition task, which is thought to be indicative of body representation [58].

All measures presented in this section are collected in RS1-RS4 from the participants with CRPS and during a single research session from healthy control participants. Hand and side of space for all tasks are coded as affected or unaffected (for controls, the “affected” and “unaffected” hand / side is coded based on their matched participant with CRPS). Each task is preceded by a short practice session to familiarise the participant with the task. If they do not appear to follow the instructions during practice, these are explained again, and the practice is repeated.

***Visuospatial attention*** The following three computer-based tests are used to measure visuospatial attention: the visual TOJ task, the Landmark task and the Greyscales task.

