*The visual TOJ task* TOJ tasks are sensitive measures of covert spatial attention, used both in clinical populations [82–88] and healthy people [89–93]. The usual procedure involves presenting pairs of identical stimuli, one on each side of space, with different onsets but the same duration. The participant’s task is to report which of the two stimuli they perceived first. According to the prior entry hypothesis [94], stimuli that are subject to greater attention are perceived earlier relative to stimuli that are subject to lesser attention. The TOJ task takes advantage of this premise. The visual variant of the TOJ used in this study is similar to that described in a previous article [8]. The participants keep their hands uncrossed on their laps under the table, and have their head stabilised by a chinrest. They are instructed to maintain their gaze on a black fixation point (3 mm in diameter), approximately 28 cm from their torso, located in the centre of a 46.5 × 35.5 cm white board laid on a table. Pairs of brief (10 ms) red light stimuli (3 mm in diameter) are presented using laser pointers controlled via an Arduino platform that is integrated with PsychoPy software [95]. The lights are presented 9 cm (approximately 18°) to the left and 9 cm to the right of the fixation point (one on each side), using a range of ten temporal offsets: ±10, ±30, ±60, ±120 and ± 240 ms (with negative numbers representing the trials in which the light on the affected side appeared first). Each temporal offset is presented 15 times in pseudorandom order, giving a total of 150 trials. To account for any response bias [96] the participants complete the TOJ task once while indicating which of the two lights appeared first, and a second time while indicating which light appeared second (order counterbalanced between participants). Participants’ verbal responses (“Left” or “Right”) are inputted via the computer keyboard by the researcher. The relative number of left-right responses to different offsets of the stimuli is re-expressed as the number of affected-unaffected responses. To derive the Point of Subjective Simultaneity (PSS) for each participant and each condition, these data are then fitted with a cumulative Gaussian using a criterion of maximum likelihood. The PSS expresses the amount of time (ms) by which the light that appears in the affected side of space should precede (negative PSS values) or follow (positive PSS values) the light that appears in the unaffected side of space for the two stimuli to be perceived as simultaneous. For the analysis, PSSs from the two response blocks (which light appeared first or second) will be averaged to obtain a single index of attention bias. A negative PSS value indicates a bias of attention away from the affected side, whereas a PSS value of 0 indicates equal distribution of attention to both sides of space.

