**Fig. 2 Fig2:**
[figure not shown]
The time course of a single trial in the Landmark task

Participants are instructed to indicate whether the left or the right landmark was closer to the fixation cross. They give their responses by pressing the green (“left”) or red (“right”) button (using the index and middle finger of the unaffected hand). The button press ends the trial and initiates the next trial. To control for response bias, in a separate, second block of the task, they are instructed to indicate which target was further away from the fixation cross by pressing the same buttons. The order of the two blocks is counterbalanced between participants. Attention bias is calculated from a relative number of “Left” and “Right” responses to each stimulus pair (landmarks position relative to the fixation cross). This is re-expressed in terms of affected versus unaffected sides of space and converted to a Point of Subjective Equality (PSE) using a cumulative Gaussian fit. The PSE expresses the relative distance at which the landmark on the affected side of space should be further from (negative PSE values) or closer to (positive PSE values) the fixation cross for the two landmarks to be perceived as appearing at equal distance from the fixation cross. A negative PSE value indicates an attention bias away from the affected side and / or under-representation of that side of space. For example, if a participant with a left-affected limb indicates that the left landmark is appearing closer to the fixation cross more often than the right landmark (i.e., underestimating distance on left side), their PSE value will be negative and indicate reduced attention to or under-representation of the left (affected) side. We will average the PSEs from the two response blocks (which landmark was closer or further away from the fixation cross) to obtain a single spatial bias index for our analyses.

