### Statistical analyses

To process and analyse the data we will use IBM SPSS Statistics [106], R [107], and MATLAB [108] software. Hypotheses will be tested using a significance level of *α* = .05. We will control type I errors in the primary analyses using Holm-Bonferroni corrections for multiple comparisons within each outcome analysis. No correction for multiple testing will be made in the exploratory analyses. We will report 95% bias-corrected and accelerated (BCa) bootstrap confidence intervals around all mean values.

Outliers are defined as scores outside ±3 SDs from the participant’s mean score for a task condition (participant-level data) or from the group mean (group-level data) for a particular test or task condition. We will examine participant-level and group-level RT data in the Hand Laterality Recognition and Directional Hypokinesia tasks for the presence of outliers and use nearest neighbour replacement if any are identified. We will use the same method of nearest neighbour replacement for the group-level outliers identified on the remaining outcome measures.

T-tests and ANOVAs will be conducted to compare mean values between groups and between data collection time points. Statistically significant interactions will be interrogated through follow-up contrasts. Wilcoxon signed-rank tests and Mann-Whitney U tests will be used if assumptions of t-tests are violated; however, ANOVAs are robust to moderate violations of normality and homogeneity of variance. Therefore, we will use ANOVAs unless severe violations of normality, homogeneity of variance, and sphericity assumptions are present, in which case we will use linear mixed models analyses with bootstrapping procedures.

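### The temporal order judgement bias score is fitted without a lapse term, so a few slips on easy trials add noise to the PSS and push a non-zero PSS outward

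*Protocol article*

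**What the plan says.** The protocol article describes the TOJ task under Computer-based/psychophysical tests. Pairs of lights are shown "using a range of ten temporal offsets: ±10, ±30, ±60, ±120 and ± 240 ms", and "Each temporal offset is presented 15 times in pseudorandom order, giving a total of 150 trials". The task is done twice, once reporting the first light and once the second. Spoken answers "are inputted via the computer keyboard by the researcher". For the point of subjective simultaneity (PSS), "these data are then fitted with a cumulative Gaussian using a criterion of maximum likelihood". Then "PSSs from the two response blocks (which light appeared first or second) will be averaged to obtain a single index of attention bias". The Landmark responses are likewise "converted to a Point of Subjective Equality (PSE) using a cumulative Gaussian fit".

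Three other provisions bear on data quality:

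- Practice: "Each task is preceded by a short practice session to familiarise the participant with the task", repeated if instructions are not followed.
- Trial-level outliers, under Statistical analyses: "We will examine participant-level and group-level RT data in the Hand Laterality Recognition and Directional Hypokinesia tasks". The TOJ is not among these tasks.
- Group-level outliers: on the remaining measures, scores beyond ±3 SD of the group mean are replaced.

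Table 3 assigns the TOJ to RQ2 to RQ5. The PSS is a secondary outcome analysed by a 2 × 4 ANOVA. The article labels its RQ4 predictor analyses, and the analyses linking neuropsychological to clinical measures under RQ5, as exploratory.

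**The concern.** A cumulative Gaussian has asymptotes of exactly 0 and 1. Under maximum likelihood, one wrong answer far from the threshold is so improbable that the curve flattens or moves to accommodate it. Slips have several routes into this task: 300 spoken answers, a reversed question in one block, a researcher keying each answer, and sessions of 2 to 4 hours with people in pain.

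The stated safeguards do not reach the problem. Practice checks understanding, not later inattention. Averaging the blocks removes response bias and some noise. The ±3 SD rule catches only extreme scores. At stake is how well a spatial-attention outcome, which bears on the proposed mechanism, separates spatial bias from inattention.

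**Working it through.** **Inputs from the article.** Ten offsets, 15 presentations each, two blocks averaged. The trial count reproduces: 10 × 15 = 150 per block. The easy offsets ±120 and ±240 ms give 4 × 15 = 60 trials per block.

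**Assumed inputs.** The article gives no lapse rate, slope or PSS. Below, λ is the chance of a wrong answer at an easy offset, set to 2% (0.02 × 60 = 1.2 slips per block) or 5% (0.05 × 60 = 3). The slope SD σ is 30, 60 or 100 ms, and the true PSS is 0, -20 or -40 ms.

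**Models compared.**

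- Plain: P = Φ((x - PSS)/σ)
- With lapses: P = λ + (1 - 2λ)Φ((x - PSS)/σ), λ estimated within 0 to 0.10

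**Step 1: the weight of one slip.** Take σ = 40, PSS = 0 and a wrong answer at -240 ms. Plain model: P = Φ(-6) ≈ 1 × 10⁻⁹, log-likelihood about -20.7. With λ = 0.02: P ≈ 0.02, log-likelihood -3.9.

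**Step 2: fixed slips in one block** (expected counts plus slips, σ = 40, plain fit).

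| True PSS | Slips | Fitted PSS |
|---|---|---|
| 0 | 1, 2, 3 at -240 | -4.7, -8.7, -12.6 |
| 0 | one at each end | 0.0 (fitted σ 88) |
| -20 | 1, 2, 3 at -240 | -29.4, -36.3, -42.4 |
| -20 | one at each end | -28.4 |
| -10 | 3 at +240 | -3.0 |

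In all of these the lapse fit stays within about 0.1 ms of the truth. A given slip can move the score either way, depending on its side. If only one block has slips, averaging halves the shift.

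**Step 3: random lapses** (Monte Carlo, two blocks averaged).

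| σ | True PSS | λ | Plain fit | Lapse fit |
|---|---|---|---|---|
| 30 | -40 | 2%, 5% | -47.1, -53.1 | about -40 to -41 |
| 60 | -40 | 2%, 5% | -43.2, -46.1 | -39.9, -39.8 |
| 30 | 0 | 5% | no material bias, SD 7.0 | SD 4.4 |
| 60 | 0 | 5% | no material bias, SD 9.0 | SD 7.2 |
| 100 | -40 | 5% | mean -42.2, RMSE 11.7 | RMSE 11.0 |
| 30 | 0 | 0 | SD 3.6 | SD 3.6 |
| 60 | 0 | 0 | SD 5.6 | SD 5.7 |

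For a true PSS of -20 with σ 30 to 60, the plain fit averages about -22 to -26; a repeat run of 1000 replicates put the upper end at -26.9. If a lapse is instead a random guess, half of which are right by luck, 5% lapses mean 2.5% wrong answers. The shift at σ 30 and PSS -40 is then smaller, to -48.4.

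The outward shift has a simple cause. Offsets within ±60 ms supply 6 × 15 = 90 of the 150 trials and largely fix the ratio PSS/σ. When slips inflate σ, the PSS is scaled up with it. A PSS of 0 stays at 0.

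**Step 4: what the extra spread costs.** At PSS 0 and 5%, measurement variance rises by (7.0/4.4)² = 2.5 at σ 30 and (9.0/7.2)² = 1.6 at σ 60. With an assumed between-person SD of 15 ms, total variance at one visit rises by (225 + 49)/(225 + 19.4) = 1.12 and (225 + 81)/(225 + 51.8) = 1.11. For changes between visits, stable between-person variance drops out, so the loss lies between these figures and the measurement ratios.

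**Step 5: association with pain** (n = 42, σ 30 or 50, no true link; lapses counted as guesses, averaging 3% and rising 2 points per SD of pain).

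| Mean PSS | Between-person SD | Mean r | Rejection at 5% |
|---|---|---|---|
| 0 | 10 | about 0 | 6-7% |
| -20 | 20 | about -0.05 | 6-7% |
| -20 | 10 | -0.08 to -0.12 | 9-13% |
| -40 | 10 | -0.14 to -0.22 | 16-29% |

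**Step 6: Landmark task.** At slope SD 0.15° (assumed) and 5% lapses, a true -0.10° becomes -0.088°. The error of 0.012° compares with a stimulus step of 0.1°.

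**The case against.** The strongest reply is that the article does not rule out a lapse term, which could sit in a fitting script or fuller document. That stands as a caution: the point concerns the method as printed, not code nobody has seen. It does not dispose of the point, because the article names both the function and the estimator, and the function named has no lapse term.

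Three stronger readings are tempting, and the documents do not support them:

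- **Slips always inflate the PSS.** With a true PSS of 0 and symmetric lapses there is no mean bias, and slips on one side can shrink a score. The outward shift is an average effect for a non-zero PSS.
- **The plan creates a false link with pain.** This needs lapses that rise with pain and a mean PSS away from zero. The article gives no figure for either, and it labels these correlations exploratory.
- **The treatment comparison is biased.** Lapses equally common in both arms create no group difference under the null, and assessment is blinded. What is shown is lost precision.

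It is also fair that practice, 15 trials per offset, two averaged blocks and the ±3 SD rule give partial protection, and that a flat psychometric slope makes the two fits nearly equivalent.

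**Conclusion.** The concern holds in a limited form. As printed, the TOJ fit has no lapse term, and no trial-level rule covers slips at its easy offsets. If wrong answers there run at 2-5% and slope SDs are 30-60 ms, the plain fit adds avoidable noise and moves a non-zero PSS outward by roughly 2 to 6 ms at a true -20 and 3 to 13 ms at a true -40. These sizes rest wholly on assumed lapse rates, slopes and PSS values. The negative PSS in those examples is the direction the article hypothesises for CRPS.

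The consequence is lost precision for one secondary outcome (RQ2) and for the exploratory RQ4 and RQ5 analyses. A reader might infer that a PSS-pain correlation from this trial would be an artefact; that follows only under the two conditions named above. The primary outcomes and sample size are untouched, and the Landmark bias is negligible. The change is worth making because it is nearly free.

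**What to change.** In the TOJ description, state that each block is fitted by maximum likelihood with P = λ + (1 - 2λ)Φ((x - PSS)/σ), with λ estimated within a small bound (for example 0 to 0.10). Then average the two PSS values as planned. Use the same form for the Landmark PSE for consistency. If a lapse term is already used, a sentence saying so and giving its bound is enough.

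The cost is one extra parameter in the fitting script. Data collection does not change, and precision without lapses is essentially the same (SD 3.6 against 3.6 ms at slope 30; 5.6 against 5.7 ms at slope 60). The term is not a complete cure for very flat slopes: at σ = 100 and true PSS -40, three slips at -240 ms in one block still give -60.7.

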**Fig. 1 Fig1:**
[figure not shown]
Representation of the stimuli in the Landmark task. White filled circles represent the stimulus pair in which the left landmark is farther from the fixation cross (− 8.1° away) and the right landmark is closer (6.9° away). Circles with dashed lines in matched colours represent other possible stimulus pair locations

**Fig. 2 Fig2:**
[figure not shown]
The time course of a single trial in the Landmark task

Participants are instructed to indicate whether the left or the right landmark was closer to the fixation cross. They give their responses by pressing the green (“left”) or red (“right”) button (using the index and middle finger of the unaffected hand). The button press ends the trial and initiates the next trial. To control for response bias, in a separate, second block of the task, they are instructed to indicate which target was further away from the fixation cross by pressing the same buttons. The order of the two blocks is counterbalanced between participants. Attention bias is calculated from a relative number of “Left” and “Right” responses to each stimulus pair (landmarks position relative to the fixation cross). This is re-expressed in terms of affected versus unaffected sides of space and converted to a Point of Subjective Equality (PSE) using a cumulative Gaussian fit. The PSE expresses the relative distance at which the landmark on the affected side of space should be further from (negative PSE values) or closer to (positive PSE values) the fixation cross for the two landmarks to be perceived as appearing at equal distance from the fixation cross. A negative PSE value indicates an attention bias away from the affected side and / or under-representation of that side of space. For example, if a participant with a left-affected limb indicates that the left landmark is appearing closer to the fixation cross more often than the right landmark (i.e., underestimating distance on left side), their PSE value will be negative and indicate reduced attention to or under-representation of the left (affected) side. We will average the PSEs from the two response blocks (which landmark was closer or further away from the fixation cross) to obtain a single spatial bias index for our analyses.

*The Greyscales task* The Greyscales task is a sensitive measure of overt spatial attention bias. The task used in the present study follows a previously developed procedure [55]. Forty pairs of short (9.95° × 1.95°) and long (12° × 1.95°) greyscale bars (Fig. 3) are presented in the centre of a white screen in a free-viewing condition until the response is given. Participants indicate if the top or the bottom bar appears overall darker by pressing the upper or lower button, respectively (using the index and middle fingers of their unaffected hand). The trials are separated by an 18° × 8° mask (random dot 1111 × 362 black and white pixel pattern of static) displayed for 150 ms, after which the next trial begins. An attention bias score is calculated by subtracting the number of “rightward” responses (choosing whichever bar is darker on its right side, regardless of its vertical position) from the number of “leftward” responses and dividing the difference by a total number of trials. Negative scores indicate rightward bias, i.e. reduced attention to the left side. This will be re-expressed as bias relative to the affected / unaffected side.

**Fig. 3 Fig3:**
[figure not shown]
Example pair of stimuli in the Greyscales task. A person who has reduced attention to the left side of space would judge the upper bar as having overall greater average darkness

***Mental representation of space*** The Mental Number Line Bisection task aims to measure spatial bias in the mental representation of space. This is based on the evidence that people implicitly represent numbers in a linear arrangement in which smaller numbers are located to the left side of space, and larger numbers are located to the right side of space [97]. The procedure is adapted from a previous study [56] in which pairs of numbers were read aloud to the participants and they were required to indicate the number that would fall midway between the two without making any calculations. The current task uses the same intervals (9, 16, 25, 36, 49 and 64) between two numbers that ranged from 2 to 98. For example, the midpoint number between 54 and 70 (16-interval) would be 62 (Fig. 4). The only deviation from the previous procedure [56] is that every pair of numbers is presented twice – once in ascending and once in descending order, to reduce response bias. There are 84 trials presented in pseudorandom order and participants’ verbal responses are inputted to the computer via the keyboard by the researcher. We subtract the subjective midpoint number from the objective midpoint number in each trial (for example, see Fig. 4), and the average score is transformed to indicate the relative bias in the mental representation of space away (negative values) or towards (positive values) the affected hand-side. A bias away from the affected side was previously found in CRPS patients on Mental Number Line Bisection [56], as well as a rightward bias in post-stroke hemispatial (left) neglect patients [81, 98–100], and a leftward bias in healthy participants (“pseudoneglect”) [56, 101, 102].

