Finally, the current study aims to explore potential predictors of the course of the disease and therapeutic response by tracking the symptoms of the same individuals over the course of 7.5 months. We plan to identify possible markers that would account for the individual differences in the progression of CRPS over time and / or in response to PA treatment. Due to insufficient evidence to support any specific predictions and limited sample size, we will perform exploratory analyses to address this research question. Factors such as demographic characteristics, pain intensity, CRPS symptom severity, sensory, motor and autonomic functions, and the extent of neuropsychological changes will be taken into consideration.
RQ 5.Are the neuropsychological changes in CRPS related to clinical signs and symptoms of CRPS?

A secondary aim of this study is to investigate the relationships between the severity of clinical symptoms of CRPS and the extent of neuropsychological changes in spatial attention, space and body representations, and motor functions.

Hypothesis: Baseline abnormalities in perception of and attention to the affected limb and its surrounding space in participants with CRPS (compared to the perception and attention of healthy control participants) will correlate with the severity of pre-treatment clinical symptoms.

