##### Relationships between neuropsychological changes and clinical symptoms of CRPS

Correlation and regression analyses will be conducted to test relationships between neuropsychological changes (as measured by computer-based tasks) and clinical symptoms of CRPS (as measured by self-report questionnaires and clinical assessments). These analyses will depend on which outcomes show significant differences between participants with CRPS and healthy controls, thus they are exploratory.

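### The Mental Number Line score is zeroed at the objective midpoint and flipped by affected side despite a healthy leftward bias, so left- and right-affected patients carry opposite offsets into the exploratory RQ4/RQ5 models

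*Protocol article*

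**What the plan says.** In the protocol article, under Computer-based/psychophysical tests (Mental representation of space), the score starts from a zero at the true midpoint: "We subtract the subjective midpoint number from the objective midpoint number in each trial". The mean over trials then "is transformed to indicate the relative bias in the mental representation of space away (negative values) or towards (positive values) the affected hand-side". The closing sentence of that paragraph, which is about the same task, reports earlier findings that include "and a leftward bias in healthy participants".

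The Temporal Order Judgement (TOJ), Landmark and Greyscales scores are also expressed about a fixed zero and re-signed by affected side. For TOJ, "a PSS value of 0 indicates equal distribution of attention to both sides of space"; for Greyscales, "This will be re-expressed as bias relative to the affected / unaffected side". The protocol states no healthy left or right bias for these three tasks. Healthy controls take the side code of the patient they are matched to.

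Under Secondary research questions and hypotheses, RQ5 predicts that baseline abnormalities ("compared to the perception and attention of healthy control participants) will correlate with the severity of pre-treatment clinical symptoms"). For the analysis, "Correlation and regression analyses will be conducted to test relationships between neuropsychological changes (as measured by computer-based tasks) and clinical symptoms of CRPS". That section calls these analyses exploratory and makes them depend on which outcomes differ from controls. The RQ4 section enters computer-based test scores as possible predictors, from an open list and again as exploratory work. Neither section mentions a control reference value or a term for affected side.

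**The concern.** The quantity in the RQ5 hypothesis is departure from healthy performance. The quantity the scoring rule produces is departure from the objective midpoint, with its sign set by the affected arm. If healthy people sit to the left of that midpoint, the two differ by an amount whose sign depends only on side.

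The direction follows from the protocol's own definitions. A leftward bias makes the subjective midpoint too small, so objective minus subjective is positive. For a left-affected patient this reads as towards the affected side. For a right-affected patient the sign is reversed and it reads as away from it. Two patients with the same normal bias and no CRPS effect therefore differ by 2m.

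In a correlation or regression among patients, this gap is a two-valued side variable added to the predictor. The cost is lost power to find a real link between spatial bias and clinical severity. If the clinical measure also varies with side, the estimate is confounded as well.

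**Working it through.** **Inputs.** From the protocol: the direction of the healthy bias (leftward), the zero point, the sign rule, 42 CRPS participants and 21 controls. Not in the protocol, and so assumed: the size m of the healthy bias in SD units of the true abnormality score (0.25 to 1.0), the true correlation (r = 0.40) and the share of patients affected on the left (q = 0.5, with 0.3 as a check). The protocol gives no figure for these correlations, so there is none to reproduce.

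**Model.** Observed score x = a + s·m, where a is the affected-side-coded abnormality (SD 1) and s is +1 for left-affected and -1 for right-affected patients. The variance of s·m is 4q(1 - q)m². If side is unrelated to severity,

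r_obs = r / sqrt(1 + 4q(1 - q)m²), which is r / sqrt(1 + m²) at q = 0.5.

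Example at m = 0.5: 0.40 / sqrt(1.25) = 0.358, and side makes up 0.25 / 1.25 = 20% of the score variance.

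**Power.** Two-sided 5%, Fisher z: Φ(atanh(r_obs)·sqrt(42 - 3) - 1.96). At r = 0.40: 0.4236 × 6.245 - 1.96 = 0.686, giving 75%.

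| m (SD) | Side share of variance | Multiplier on r | r_obs | Power, q = 0.5 | Multiplier, q = 0.3 |
|---|---|---|---|---|---|
| 0 | 0% | 1.00 | 0.400 | 75% | 1.00 |
| 0.25 | 5.9% | 0.97 | 0.388 | 73% | 0.975 |
| 0.5 | 20% | 0.89 | 0.358 | 65% | 0.91 |
| 0.75 | 36% | 0.80 | 0.320 | 54% | 0.82 |
| 1.0 | 50% | 0.71 | 0.283 | 44% | 0.74 |

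**False association.** Set the true r to 0 and let severity differ by d SD between sides (residual SD 1, q = 0.5). Then r = 0.5·m·d / sqrt((1 + d²/4)(1 + m²)). With d = 0.5, r is 0.06, 0.11 and 0.17 at m = 0.25, 0.5 and 1.0. The rejection rates are 7%, 10% and 19% instead of 5%. With d = 0, r is 0 and no false association arises.

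**Effect of the remedies.** Simulation with 6000 runs, 21 left- and 21 right-affected patients, true r = 0.40, and 21 controls with SD 1. Each cell gives mean r and power.

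| m (SD) | As scored | Centred on control mean, then flipped | Adjusted for affected side |
|---|---|---|---|
| 0 | 0.393 / 75.3% | 0.385 / 73.8% | 0.393 / 74.5% |
| 0.5 | 0.355 / 66.3% | 0.390 / 75.5% | 0.398 / 76.1% |
| 1.0 | 0.277 / 44.7% | 0.387 / 74.5% | 0.395 / 75.3% |

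The small loss from centring is the sampling error of the control mean: 1/sqrt(21) = 0.22 SD, a multiplier of about 1/sqrt(1 + 0.048) = 0.977.

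**Where the offset cancels.** In the CRPS-versus-control mean contrast, the residual offset is 2m times the difference in left-affected share between the groups. It is zero if the shares match, and 2m(21/42 - 12/21) = -0.14m if, for example, 12 of 21 controls are coded left. In the treatment comparisons, a constant offset drops out of within-person change, and affected arm is a minimisation factor.

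**The case against.** The strongest reply is that the protocol has not fixed these models. Both sets of analyses are exploratory, the RQ4 predictor list is open, affected arm is recorded for every patient, and nothing excludes it as a covariate. An unwritten covariate in such a model is normally left to an analysis plan. That is fair, and a missing covariate alone would be no finding. What stands is the scoring rule. It is written down, it sets the zero at the objective midpoint, and it sits beside a statement that healthy people are not at that zero.

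A second reply is that only tasks differing from controls are to be carried into the RQ5 correlations, so a task showing nothing but the normal bias would usually drop out. This narrows when the problem matters. It does not remove the offset from a task that passes.

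Third, m is unknown, and at 0.25 SD the loss is trivial. This is correct, and it is why the priority is low.

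Three stronger readings are tempting, and the protocol does not support them:

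- A reader might infer that all four lateral bias scores are offset, because they share the coding. The healthy leftward bias is stated for the number-line task only.
- A reader might infer that the coding manufactures correlations. On its own it only weakens them. Grip ratio is one listed measure where a side component is plausible: the protocol allows for a normal difference between dominant and non-dominant hands, so a right-hander affected on the left would tend to have a lower ratio and a more towards-affected number-line score. That runs against the expected association and would tend to mask it.
- A reader might infer that individual patients will be misclassified as biased away from the affected side. No planned analysis classifies individuals on these four tasks.

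**Conclusion.** The point holds for Mental Number Line Bisection, in the RQ4/RQ5 correlations and regressions among CRPS patients. On the protocol's own statements, left- and right-affected patients carry offsets of +m and -m that have nothing to do with CRPS, and the score entered is not the control-referenced abnormality that RQ5 names.

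The consequence is attenuation ranging from negligible to large: a multiplier on r of 0.97 at m = 0.25 SD down to 0.71 at m = 1 SD. This rests on assumed values of m, r and the side split, and on n = 42. The RQ4 response model uses the PA group only, with 21 planned, so its power is lower throughout; the multiplier depends on m and the side split, not on n.

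It would be wrong to conclude that the trial's main results are at risk. Pain, CRPS severity score, the sample size and the RQ2 treatment comparisons are not affected, and matched-side coding of controls largely protects the RQ5 mean contrasts. This is a minor, inexpensive improvement to exploratory analyses.

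**What to change.** For RQ4 and RQ5, subtract the healthy-control mean of the raw left/right Mental Number Line score from each patient's raw score, and only then re-sign by affected side. Zero then means normal, as the RQ5 hypothesis requires. Apply the same step to the TOJ, Landmark and Greyscales scores as a precaution; if controls show no bias there, little changes.

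An alternative is to include affected side as a covariate in each model that uses these scores. This is not equivalent: it also removes any genuine CRPS-related difference between left- and right-affected patients, whereas centring removes only the healthy bias as estimated from the controls. State which is chosen before these analyses are run.

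The cost is one line of scoring code plus the sampling error of a mean from 21 controls, or one degree of freedom per model for the covariate. The control data and the affected side are already being collected.
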